### Randomization

At the end of the pre-intervention visit, participants will be randomly allocated to one of the two groups. The randomization sequence generation will be performed by an independent research assistant using a computer random number generator while the allocation sequence concealment will be performed using sequentially numbered, opaque and sealed envelopes. To ensure good balance of factors known to affect the natural history of pregnancy-related LBPP in our small sample, two minimization criteria will be considered: baseline pain intensity and baseline physical activity levels. Participants will not be blinded to intervention allocation, but the content of the exercise sessions will be shared only to those randomized to the intervention group to prevent cross-contamination between groups. The kinesiologist who will prescribe and supervise the exercise sessions will not take part in the pre- and post-intervention evaluations. The member who is running the pre- and post-intervention evaluations and who is managing the database, as well as the person who is supervising the exercise sessions, are not blinded. Members of the research team involved in statistical analyses will be blinded to group allocation.

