#### Secondary outcome measures

The potential effectiveness of the intervention will be assessed using the following clinical outcomes and assessment tools. All secondary outcome measures (i.e., LBPP incidence, frequency and intensity, functional disability and physical activity levels) will be obtained during the pre-intervention (≤ 20 weeks of gestation) and post-intervention (34–36 weeks of gestation) visit at the university laboratory. Fear avoidance behaviors the level of anxiety, and depression will also be assessed pre- and post-intervention, as they are considered potential prognostic factors (and confounding variables) of LBPP [38].

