### Statistical analysis

Demographic data will be presented using means and standard deviations. For primary outcome measures (recruitment, retention, adherence rate, safety, and acceptability), means, standard deviations and/or percentage will be presented. For secondary outcomes measures, descriptive statistics will be used to describe within-group changes from baseline visit to post-intervention visit (34-36 weeks of pregnancy). Differences between group in mean change with confidence intervals and effect sizes (Cohen’s *d*) will be reported for each measure.

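### The between-group effect is a raw difference in mean change; ANCOVA on baseline and the minimisation factors would usually give narrower intervals from the same data

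*Protocol article*

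**What the plan says.** The Statistical analysis section has two parts for secondary outcomes. Within groups, "descriptive statistics will be used to describe within-group changes from baseline visit to post-intervention visit". Between groups, it commits to "Differences between group in mean change with confidence intervals", plus Cohen's d, for each measure. No covariate or regression model is named.

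The Randomization section states that "two minimization criteria will be considered: baseline pain intensity and baseline physical activity levels". The reason given is prognostic: "To ensure good balance of factors known to affect the natural history of pregnancy-related LBPP in our small sample". Neither factor is mentioned again in the analysis.

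The baselines needed for adjustment are already scheduled. Under Secondary outcome measures, the pain, disability and activity outcomes "will be obtained during the pre-intervention (≤ 20 weeks of gestation) and post-intervention (34–36 weeks of gestation) visit". Fear avoidance, anxiety and depression are measured at the same two visits, "as they are considered potential prognostic factors (and confounding variables) of LBPP".

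The Sample size section sets 20 women per arm from recruitment capacity and a rule of thumb. It wants the trial to supply a variance for planning the full-scale study, and intends to size that study from post-intervention group differences in pain and disability.

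**The concern.** A difference in mean change subtracts the whole baseline value. That is the best use of the baseline only if the regression of follow-up on baseline has slope 1. If the slope is smaller, the change score over-corrects: a chance baseline difference between arms returns in the estimate through regression to the mean, and the interval is wider than it need be.

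Minimisation adds to this. Balancing on prognostic factors and then leaving them out of the model keeps their variance in the standard error, so precision gained at allocation is not shown in the interval. Minimisation also acts directly only on pain and physical activity. Baselines of the Pelvic Girdle Questionnaire, kinesiophobia, anxiety and depression scores are balanced only as far as they correlate with those two factors.

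What is at stake is the precision of the effect estimates, and the usefulness of the variance that this trial is meant to hand to the next one.

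**Working it through.** **Inputs.** From the article: 20 women per arm; a retention criterion of at least 80%, hence 16 per arm at the limit; a pain MCID of 18–19 mm on the VAS. Assumed, because the article does not give them: the baseline-to-follow-up correlation r, the ratio k of follow-up SD to baseline SD, and a VAS SD of 20 mm for illustration. There is no power calculation to reproduce; the total is simply 20 + 20 = 40.

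**Large samples, any SD ratio.** In units of the baseline variance, the per-woman variances are:

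- change score: 1 + k² − 2kr
- ANCOVA: k²(1 − r²)

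The difference is (1 − kr)², which is never negative. In large samples ANCOVA is therefore never less precise, and the two tie when kr = 1. With k = 1 the variance ratio, ANCOVA to change score, is (1 + r)/2: 0.65, 0.75 and 0.85 at r = 0.3, 0.5 and 0.7.

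**At this sample size, k = 1.** Expected 95% half-widths in outcome-SD units, with N = 2n:

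- change score: t(N−2) × √(2(1−r)) × √(2/n)
- ANCOVA on own baseline: t(N−3) × √(1−r²) × √(2/n) × √(1 + 1/(N−4))

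| r | Change score, n = 20 | ANCOVA, n = 20 | Ratio, n = 20 | Ratio, n = 16 |
|---|---|---|---|---|
| 0.3 | 0.757 | 0.620 | 0.82 | 0.82 |
| 0.5 | 0.640 | 0.563 | 0.88 | 0.88 |
| 0.7 | 0.496 | 0.464 | 0.94 | 0.94 |
| 0.9 | 0.286 | 0.283 | 0.99 | 0.99 |
| 0.95 | 0.202 | 0.203 | 1.00 | 1.01 |

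With an SD of 20 mm and r = 0.5, the half-width at 20 per arm falls from ±12.8 mm to ±11.3 mm. Comparing follow-up values alone gives 0.640 SD, so with equal SDs and r = 0.3 the change score (0.757) does worse than not using the baseline at all.

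**Effect of unequal SDs, large samples, r = 0.5.**

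- k = 0.75: 0.422/0.8125 = 0.52; √0.52 = 0.72, about 28% narrower
- k = 1: 0.75/1 = 0.75; about 13% narrower
- k = 1.5: 1.6875/1.75 = 0.96; about 2% narrower
- k = 2: 3/3 = 1.00; no gain

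**Chance imbalance.** For a baseline that is not balanced by design, the SD of the difference between arms is √(2/20) = 0.32 SD. At r = 0.5 and k = 1, an imbalance of that size shifts the change-score contrast by (1 − 0.5) × 0.32 = 0.16 SD. ANCOVA removes this shift.

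**Adding the minimisation factors.** A simulation of 40 women (4,000 runs per scenario) minimised on two dichotomised factors with an assumed 0.8 biased coin. Mean half-widths:

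| Scenario | Change score | ANCOVA | ANCOVA + factors |
|---|---|---|---|
| r = 0.5, factors modestly prognostic | 0.637 | 0.560 | 0.541 |
| r = 0.7, factors modestly prognostic | 0.494 | 0.461 | 0.436 |
| r = 0.5, factors not prognostic | 0.635 | 0.556 | 0.565 |
| r = 0.9, factors not prognostic | 0.285 | 0.281 | 0.286 |

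With modestly prognostic factors, the full model is narrower than the change score by 1 − 0.541/0.637 = 15% and 1 − 0.436/0.494 = 12%. With non-prognostic factors, adding them costs 0.565/0.556 = 1.02, about 2%. Coverage of the change-score interval was 94.8% to 96.0% across all scenarios run.

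**The case against.** The strongest reply is that this is an efficiency preference in a feasibility trial. The primary outcomes are recruitment, retention, adherence, safety and acceptability. No progression criterion uses a between-group effect, and effectiveness is reported without tests. An article's short analysis paragraph may also leave covariates to a fuller document. All of that limits the weight of the point. It does not remove it, because the paragraph does name an estimator, and a better one is available from data already collected.

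Four stronger readings are tempting, and the documents do not support them:

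- *The plan ignores the baseline.* It does not. A change score uses the baseline with a coefficient of 1. The word unadjusted does not appear in the article either; it is the plain reading of a sentence that names no covariate.
- *Every interval is too wide.* The gain disappears at r near 0.9 to 0.95, or at r = 0.5 when the follow-up SD is twice the baseline SD. Non-prognostic factors cost a little. LBPP incidence, defined as the first episode in pregnancy, is not a mean change.
- *The correlation must be modest because pain-free and painful women are mixed.* Mixing also widens the baseline spread, which could raise the correlation. The article gives no value.
- *The change-score SD is the wrong variance for the main trial.* That holds only if the main trial uses ANCOVA, which the article does not state. Nothing prevents the residual SD from being computed later from the same data.

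For pain and physical activity, minimisation already limits the baseline imbalance described above.

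**Conclusion.** The point holds as a modest loss of precision. The stated estimator fixes the baseline coefficient at 1 and omits the two factors that the trial itself treats as prognostic. For most continuous secondary outcomes, a baseline-adjusted analysis would give intervals about 6% to 18% narrower. That range assumes equal baseline and follow-up SDs, correlations of 0.7 down to 0.3, and 16 to 20 women per arm. Outside those assumptions the gain may be larger or nil.

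The change-score intervals are not invalid: simulated coverage was nominal or slightly above. The feasibility outcomes and progression criteria are untouched. The change is worth making because it costs almost nothing and serves the article's stated aim of supplying a variance for the next trial.

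**What to change.** Replace the between-group sentence in the Statistical analysis section with text to this effect:

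> For each continuous secondary outcome, post-intervention values will be compared between groups by ANCOVA, adjusting for the baseline value of that outcome and for the two minimisation factors as used in allocation. Where a minimisation factor is itself the baseline of the outcome, it will be entered once. The adjusted mean difference with its 95% confidence interval will be reported, with the residual SD and the baseline-to-follow-up correlation for planning the full-scale trial. Within-group changes will be presented descriptively.

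The Randomization section does not say which instruments or cut-points define the two factors, so the wording should refer to them as used in allocation and not presume the VAS and PPAQ scores. LBPP incidence stays outside this change.

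The cost is one to three degrees of freedom and, where a factor does not predict the outcome, a widening of about 2% relative to ANCOVA on baseline alone. No visit, questionnaire or participant is added.

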### Progression criteria

The following criteria must be met in order to consider progression to a main RCT:Recruitment criteria: recruitment rate of 40 eligible women over a 12-month period.Retention criteria: retention rate of ≥ 80% of recruited women.Adherence criteria: adherence rate of ≥ 75% to the supervised and unsupervised exercise sessions.Safety criteria: less than 25% of women experiencing acute LBPP flare-ups interfering with daily activities.

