One important risk factor for developing LBPP during pregnancy is having a history of LBPP [15]. Furthermore, early LBP in pregnancy appears to be a predictor for long-term PGP [2]. Interestingly, a comprehensive review reported that the mean prevalence of postpartum LBPP was higher in studies of pregnant women with a history of LBP (42.7%) compared to when they were excluded from studies (24.3%) [5]. It is therefore of paramount importance to gain knowledge on these women because the literature shows that pregnant women with a history of LBPP have a threefold increased risk to develop LBPP during their pregnancy compared to pregnant women without a history of LBPP [5].

Despite its high prevalence, LBPP during pregnancy is often considered a common and almost natural phenomenon which often leads to inadequate clinical prevention and treatment of the condition [16]. LBPP has negative repercussions on sleep, social and sexual life, physical and work capacity, as well as on psychological health [17, 18]. Importantly, LBPP also contributes to physical inactivity during pregnancy [19], which has been associated to a higher incidence of maternal and neonatal complications [20–23]. Despite the frequent occurrence of LBPP during pregnancy and the significant impact it can have on the women’s quality of life, there are currently no specific guidelines available to inform clinical prevention and treatment of this condition. Not surprisingly, several studies indicate that about 25 to 30% of women suffering from LBPP self-manage or seek a wide range of interventions delivered by various care providers to prevent and treat their symptoms [24, 25]. However, the evidence regarding these interventions is limited due to restricted availability of high-quality studies and very low evidence strength [26, 27]. It is therefore essential to identify effective clinical strategies to prevent and treat pain and disability, while considering the safety of both the mother and growing fetus.

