### Data collection

#### Primary outcome measures

##### Feasibility components: recruitment, retention, adherence rate, safety of the intervention, and acceptability

The feasibility of recruitment, evaluated for both groups at the pre-intervention visit, will be defined as the ability to recruit eligible women throughout a 12-month period. The feasibility of obtaining a successful retention rate and consequently low attrition will be assessed using the completion of pre- and post-intervention questionnaires (see below). Adherence to the protocol will be defined as attendance to the supervised group exercise sessions and completion of the unsupervised home exercise sessions. The retention and adherence rates will be evaluated for the intervention group at the post-intervention visit. Safety of the intervention will be determined based on the number of adverse events, which will be defined as symptom flare-ups that will prevent a woman from taking part in subsequent exercise sessions or injuries requiring medical attention. In addition to the kinesiologist taking note of any undesirable effects during supervised exercise group sessions, women from the intervention group will be asked to report, via weekly text messages and their web-based diary, any reaction or flare-up that is not consistent with their usual pain presentation as a result of either home exercise or supervised group exercise sessions. Information concerning adverse events will be collected for the intervention group on a weekly basis throughout the study. Acceptability of the intervention, assessed for the intervention group at the post-intervention visit, will be determined based on how the intervention will be perceived by pregnant women (including satisfaction, practicality and accessibility assessed using 5-point Likert scales).

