***Secondary outcomes measures***				
***LBPP incidence, frequency and intensity***		X	X	X
***Functional disability***		X		X
***Physical activity levels***		X		X
***Fear avoidance behavior***		X		X
***Anxiety***		X		X
***Depression***		X		X

Pre-intervention visit (≤ 20 weeks of gestation); throughout the study (between pre-intervention and post-intervention visits); post-intervention visit (34–36 weeks of gestation)

^a^Standard prenatal care

^b^Motor control exercise program at UQTR and at home as well as standard prenatal care

^c^Intervention group only

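### The safety progression criterion counts a different event from the protocol's own safety outcome, leaves out injuries, and does not state its arm or denominator

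*Protocol article*

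**What the plan says.** Three places in the protocol article describe the safety event.

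- **Primary outcome measures, feasibility components.** Safety is judged on the number of adverse events, defined as "symptom flare-ups that will prevent a woman from taking part in subsequent exercise sessions or injuries requiring medical attention".
- **Same section, weekly self-report.** Intervention women report "any reaction or flare-up that is not consistent with their usual pain presentation as a result of either home exercise or supervised group exercise sessions".
- **Progression criteria.** The safety gate is "less than 25% of women experiencing acute LBPP flare-ups interfering with daily activities". It is one of four gates, introduced by "The following criteria must be met in order to consider progression to a main RCT".

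On who is observed, the text says "Information concerning adverse events will be collected for the intervention group on a weekly basis throughout the study", and footnote c of Table 1 marks safety as "Intervention group only". The gate itself says only women, without an arm or an analysis set.

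Weekly texts on LBPP incidence, number of days and intensity are described for participants generally (LBPP incidence, frequency, and intensity section), and Table 1 shows that row without the intervention-only footnote.

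**The concern.** A progression gate should be scored on the outcome that the protocol defines and collects. Here the two differ. A woman can miss sessions because of a flare-up while her daily life is unaffected, or have her daily life disrupted and still attend. The second limb of the definition, "injuries requiring medical attention", has no counterpart in the gate. The weekly prompt adds a condition found in neither of the others: the reaction must be unlike the woman's usual pain and must result from exercise.

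Two things are at stake. First, the team will have to choose after the fact which event and which denominator to score, and the choice may decide the gate. Second, the gate does not ask about cause, and the women are selected for a raised risk of LBPP. Some may be in pain at entry. Flare-ups that belong to advancing pregnancy could therefore be charged to the programme, with no control rate for the same event to set beside them.

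**Working it through.** **1. The three wordings side by side**

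| Feature | Safety outcome | Weekly prompt | Progression gate |
|---|---|---|---|
| Flare-up counted if | it stops later sessions | it is unlike usual pain | it is acute and disrupts daily activities |
| Injury needing medical care | yes | not named | no |
| Attribution to exercise | not stated | yes | no |
| Arm | intervention | intervention | not stated |
| Unit | number of events | each report | percentage of women |

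No column maps onto another. The described sources are the diary and texts (compliance, adverse events, LBPP incidence, frequency and intensity, treatment received) and the kinesiologist's notes of undesirable effects. None is said to ask about interference with daily activities. The Pelvic Girdle Questionnaire has an activity subscale, but it is completed only at the pre- and post-intervention visits, so it cannot count acute flare-ups between them.

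**2. The gate in counts**

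The protocol attaches no derivation to the 25%, so there is no figure to reproduce. The rule passes if x/n < 0.25:

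- n = 20 (randomised intervention women): 4/20 = 20% passes and 5/20 = 25% fails, so at most 4.
- n = 16 (80% of 20 retained): 3/16 = 18.75% passes and 4/16 = 25% fails, so at most 3.
- n = 40 (both arms): 9/40 = 22.5% passes and 10/40 = 25% fails, so at most 9.

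**3. Chance that a harmless programme fails**

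Assume that exercise adds no risk, that every activity-limiting flare-up counts, and that a proportion p of women would have one anyway. The protocol gives no value of p. Its figure of about 50% is for any low back or pelvic girdle pain in pregnancy, and its threefold risk concerns developing LBPP. So p is an assumption, shown over a range. For n = 20:

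P(fail) = 1 − Σ(k = 0 to 4) C(20, k) p^k (1 − p)^(20 − k)

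| Assumed p | P(pass) | P(fail) |
|---|---|---|
| 10% | 0.957 | 0.043 |
| 15% | 0.830 | 0.170 |
| 20% | 0.630 | 0.370 |
| 25% | 0.415 | 0.585 |
| 30% | 0.238 | 0.762 |
| 40% | 0.051 | 0.949 |

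The denominator matters too. At p = 20%, P(fail) is 0.402 with n = 16, 0.370 with n = 20 and 0.268 with n = 40.

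**4. Precision of the observed percentage**

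Exact (Clopper-Pearson) 95% intervals are 5.7% to 43.7% for 4/20, which passes, and 8.7% to 49.1% for 5/20, which fails.

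**5. What a control comparison could carry**

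With 20 women per arm and a common rate p, the approximate 95% half-width for the difference is 1.96 × √(2p(1 − p)/20). This is 0.248 at p = 20% and 0.310 at p = 50%, or about 25 to 31 percentage points. That is usable as description but too wide for a go/no-go rule.

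**The case against.** Several stronger readings are tempting, and the document does not support them.

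- **The trial would go ahead despite injuries.** The gates are conditions for considering progression, so meeting them does not oblige anyone to proceed. Injuries stay in the primary safety outcome and would be reported with it. What stands is narrower: they do not enter the gate.
- **The criterion cannot be computed.** The diary and text items are not reproduced in this condensed article. The fair statement is that no item for daily-activity interference is described.
- **The rule will probably fail on natural course.** Nothing gives the rate of acute, activity-limiting flare-ups, and women with severe disabling pain are excluded. At a 10% rate the chance of failing is only 4%. If the gate were scored from the weekly prompt, self-attribution to exercise would filter out some background pain. The Progression criteria section does not say that it is scored that way, so the possibility remains but its probability is unknown.
- **Intervention-only collection is an error in itself.** A flare-up that stops exercise sessions has no counterpart in controls, who have no sessions, so the choice fits the defined outcome. It does not fit the event in the gate, which controls can have.
- **Obstetric events must count.** The Background phrase "while considering the safety of both the mother and growing fetus" is a general remark about identifying clinical strategies and commits the trial to no data item.

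The mismatch in wording and the missing injury limb survive all of these.

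**Conclusion.** The point holds as an internal inconsistency in a decision rule. The safety outcome, the weekly prompt and the gate describe three different events, the gate omits injuries, and its arm and denominator are open. These conclusions come from the text and need no assumed figure.

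The effect of background pain is conditional. With 20 women, all such flare-ups counted and no added harm, the chance of failing runs from 4% at an assumed background rate of 10% to 76% at 30%. The figures show that the rule is sensitive to an unknown rate. They do not predict failure.

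**What to change.** 1. Reconcile the Primary outcome measures and Progression criteria sections so that one safety event, including injuries requiring medical attention, is defined, collected and used in the gate. List its components separately.
2. State the arm and denominator, for example women randomised to the intervention group with at least one event.
3. Have the investigators confirm the threshold for the reconciled event. If the event becomes broader while 25% is kept, more women will count and a harmless programme becomes more likely to fail. The clinical limit is theirs to set.
4. Report the percentage with an exact 95% confidence interval.
5. Add an item on flare-ups that interfere with daily activities to the weekly texts in both arms, and amend Table 1 to match. Read the intervention rate against control descriptively, not as a go/no-go criterion. Attribution to exercise can remain an extra item for the intervention group.

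The cost is a short amendment and one brief weekly item for controls. Recruitment began in April 2021, so the new item will be missing for follow-up already completed, and the report should say so.
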